# **Consultancy: “Social Pulse: skills, perceptions and time use in the Peruvian health sector”**

**Project # RG-T3296**

## **Rationale and background information**

The Peruvian health system is highly fragmented within the public and private sector, The Ministry of Health is the largest provider of care, providing services to around 70% of the population. Quality of care of public health services is perceived to be low both regarding human and physical capital. Human resources in the public sector are highly regulated, from working hours, compensation schemes and other contractual characteristics. In recent years, health worker unions have succeeded in having their salaries increased with strike threats claiming real wages had been decreasing in over 20 years. However, evidence of health worker performance is lacking, making it difficult to assess the regulatory efficiency concerning human resources in the public sector. Moreover, technological changes worldwide, growth and development trends and sustainability issues are rapidly changing workplaces, both in the private and public sector. There is growing evidence to suggest that there is a demand for new job skills and the need to identify these skills, especially in complex work environments. The public health sector is challenged with adapting to technological changes while being constrained by its own regulations.

## **Aim of the study**

The study aims to assess how health workers (doctors, nurses, and midwives) use their time during a regular work day and to assess health workers’ perceptions of their own skills as well as the skills people in their positions will need to fulfill their jobs in the future.

## **Methods**

### **• Study Design**

The study will be a cross-sectional observational study.

### **• Population**

We will work in Lima, the capital city of Peru, which has 1/3 of the population in the country and with a total of 369 primary health establishments managed by 4 different Health Directions: DIRIS North, DIRIS Center, DIRIS East and DIRIS south. Primary health establishments are divided into four types from lowest to highest level and number of establishments:

- Health posts type I-1 (5)
- Health centers type I-2 (156)
- Health centers type I-3 (176)
- Health centers type I-4 (32)

The Ministry of Health in Lima oversees all hospitals located in the 4 areas: 18 hospitals and 7 specialized hospitals (institutes). Our population universe will be all doctors, nurses and midwives working (regardless of the type of contract) in health centers types I-2, I-3, I-4, and general hospitals, a total of 382 facilities.

We classify doctors, nurses and midwives as defined by Law 23536 passed in 1982. This Law regulates the classification of health worker professionals, where 11 health professions are considered; doctors, nurses and midwives among them. The definitions of the medical, nurse and midwife professions recognized by law match those considered in the WHO classification of health workers as medical practitioners, nursing professionals, and midwifery professionals respectively.

The following table summarizes the number of facilities and distribution of health workers across health centers and hospitals in all four administrative areas:

| Area      | Category | Doctors | Nurses | Midwives |
|-----------|----------|---------|--------|----------|
| CENTER    | I-2      | 34      | 42     | 30       |
|           | I-3      | 357     | 217    | 136      |
|           | I-4      | 50      | 24     | 32       |
| EAST      | I-2      | 44      | 51     | 39       |
|           | I-3      | 124     | 112    | 111      |
|           | I-4      | 52      | 32     | 36       |
| NORTH     | I-2      | 44      | 72     | 52       |
|           | I-3      | 192     | 218    | 145      |
|           | I-4      | 183     | 195    | 163      |
| SOUTH     | I-2      | 80      | 119    | 86       |
|           | I-3      | 160     | 115    | 98       |
|           | I-4      | 279     | 126    | 163      |
| HOSPITALS | II-1     | 245     | 211    | 75       |
|           | II-2     | 345     | 358    | 123      |
|           | II-E     | 108     | 107    | 26       |
|           | III-1    | 3389    | 3190   | 371      |
|           | III-2    | 1744    | 2266   | 203      |

For those with full-time permanent contracts, all three professional cadres in their capacity as care providers, must work six hours a day or 36 hours a week, with a maximum of 150 hours a month. They can also fulfill day or night shifts in emergency services, hospitalization and intensive care units, which must not exceed 12 hours, or 24 hours if needed. While day or night shifts are accounted within the 150-hour limit, health professionals receive bonuses for being assigned to shifts. Doctors can work part time if they split their duties with teaching activities within the health center or hospital.

These provisions apply for health workers with full-time permanent contracts (Legislative Decree 1156), whose salaries are also regulated by law. It guarantees job security until retirement among other benefits. Health centers or hospitals offer permanent positions through open public contests, and after five years health professionals have the option to apply for promotions. Not all health professionals are hired for permanent positions and more flexible contracts are offered within each health center or hospitals at the discretion of the administrative units in charge.

## **Phases**

### **a. Design of the instruments:**

#### **a.1. Design of the instrument for direct observations of the providers (time and motion study)**

Given the absence of a standardized time and motion protocol for assessing health worker time allocation, an important phase of the study will include an exploration of the literature, contact with experts and the design of an instrument. We will also evaluate the best alternatives for the collection of data (e.g. app-based). This phase includes a targeted review of the relevant literature on time and motion studies to identify best practices in data collection instruments and methods. The literature review will be conducted using PubMed, LILACS, and targeted searches of multilateral organizations including the World Bank, World Health Organization, and USAID. We will focus on time and motion studies (possible synonyms: workflow, clinician observation) conducted since 2005 with an explicit goal of capturing the content and timing of health care worker activities. Based on our findings, we will develop an instrument, select the most appropriate method for collecting data and perform the programming or adaptations needed for the instrument to be applied with cellphones or tablets, if needed.

#### **a.2. Design of the skills-questionnaire to explore perceptions of actual skills and skills needed by health providers**

As above we will explore the literature in order to design the instrument. The questionnaire would last no more than 20 minutes. It would largely focus on the importance of various abilities and skills. We will adapt the questionnaire to an electronic version to apply it through cellular phones or tablets, if needed.

### **b. Pilot of the content of the instruments**

Instruments will be tested at a randomly selected hospital and health center. Pilot testing will include post-test interviews with field workers and with interviewees as necessary regarding any concerns or confusion about the study. Pilot data will be transmitted and analyzed for coherence, consistency, and completeness. Tools will be modified as needed based on the results of the pilot study.

### **c. Sampling**

c.1 We will conduct sampling in two stages, first selecting the health facilities and then sampling 1 of each provider type within facility; this will yield three samples (doctors, midwives, and nurses) of independent and identically distributed observations. In stage 1, we will sample from the 208 primary facilities (I3 and I4) with probability proportionate to facility distribution by tier. We will confirm that the final sample includes facilities with INFORHUS and those without. Separately, we will select two general hospitals.

In the second stage, we will request from the Ministry of Health the list of all health providers working at each health facility as well as the monthly schedule of work with basic information regarding health care worker type of contract, length working at the establishment, and similar details typically found in the National Registry of Health Personnel (INFORHUS) database. INFORHUS is an online registry in which all

institutions in the health sector must record detailed information about their employees regardless of position and type of contract. Within each sampled facility, we will confirm the schedule for the coming week with the facility manager or obtain a schedule for the week for those facilities not covered by INFORHUS. We will randomly sample two shifts from this schedule, the first as the intended observation and the second as a replacement in case a provider declines to participate, and will sample one provider of each type within the selected shifts.

We calculate sample size sufficient to provide a confidence interval of width  $\pm 3\%$  around the primary outcome of time spent on direct patient care. Drawing from existing literature on time-motion observations, we estimate standard deviation in this outcome up to 10%, which results in a sample of 54 providers per tier at primary care level. The table below shows expected distribution of health facility types in the final sample.

| Área               | Category | Total | Sample |
|--------------------|----------|-------|--------|
| Lima Metropolitana | I-3      | 176   | 35     |
|                    | I-4      | 32    | 19     |
|                    | II y II  | 24    | 2      |
| TOTAL              |          | 232   | 56     |

Note that we will sample 5 providers of each type within the hospitals for a total sample of 56 facilities and 192 observations.

c.2 We will additionally apply the skills-questionnaire to the directors of DIRIS (4), Health establishments (45) and Hospitals (2).

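### The 54 providers described as a per-tier sample are the per-cadre total over both primary tiers (35 + 19), so ±3% does not hold for one cadre within one tier

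*Combined protocol and SAP*

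**What the plan says.** All of this is in section c. Sampling, part c.1, unless noted.

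- **Design:** the plan describes "first selecting the health facilities and then sampling 1 of each provider type within facility" and adds that "this will yield three samples (doctors, midwives, and nurses) of independent and identically distributed observations".
- **Precision target:** "We calculate sample size sufficient to provide a confidence interval of width" ±3% around the primary outcome, time spent on direct patient care. No confidence level is given.
- **Variability:** "we estimate standard deviation in this outcome up to 10" percent.
- **Conclusion drawn:** "which results in a sample of 54 providers per tier at primary care level".
- **Table:** 35 of 176 I-3 facilities, 19 of 32 I-4 facilities and 2 hospitals.
- **Total:** "we will sample 5 providers of each type within the hospitals for a total sample of 56 facilities and 192 observations".

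No formula, finite-population correction or allowance for non-response is shown; a replacement shift is drawn in case a provider declines. Section f.2 (Time and motion study) plans comparisons between groups such as facility tier and provider cadre.

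**The concern.** The sentence and the table cannot both be right for a single cadre. At one provider per cadre per facility, 54 in each tier would need 54 I-4 facilities, and only 32 exist. The stated inputs do not lead to 54 either.

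This is the plan's only sample-size justification for the primary outcome, and it attaches the ±3% to tier. A reader who takes it at its word would credit a cadre's result in I-4 with precision that 19 providers cannot give.

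**Working it through.** **Inputs.** SD = 10 points, half-width d = 3 points, and the facility counts come from section c. Sampling. Provider counts come from the staffing table under Population. Assumed: two-sided 95% confidence (z = 1.96). The within-facility correlation (ICC) is not given, so I use a range of 0 to 0.3.

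**1. What 54 counts.** 35 + 19 = 54 per cadre. Total: 54×3 + 2×5×3 = 162 + 30 = 192, as stated. Read as 54 per tier per cadre, the total would be 108×3 + 30 = 354 observations.

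**2. Size from the stated inputs.** n0 = (1.96×10/3)² = 42.7, so 43 (46 using t).

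**3. Reproducing the split.** Apply n = n0/(1 + n0/N) with N as the number of facilities:
- I-3: 42.68/(1 + 42.68/176) = 34.4, so 35
- I-4: 42.68/(1 + 42.68/32) = 18.3, so 19

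Using n0 − 1 in the denominator gives 34.5 and 18.5, hence the same integers. No other variant tried gives this split. Allocating 54 in proportion to facility numbers gives 54×176/208 = 45.7 and 54×32/208 = 8.3.

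**4. Is that correction valid here?** With one provider per cadre per facility, sampling a fraction f of the facilities removes only variance between facility means. If B is the share of variance lying there, the variance of the tier mean is (SD²/n)(1 − f·B). Reaching ±3 requires B = [1 − 9/(1.96²×100/n)]/f:
- I-3 (f = 35/176): 0.91
- I-4 (f = 19/32): 0.93

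With the correction based instead on providers (I-4: 564 doctors, 377 nurses, 394 midwives), the required n is still about 38 to 41 per tier.

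**5. Half-widths at SD 10%.**

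| Estimate | n | z | t |
|---|---|---|---|
| One cadre, I-3 | 35 | 19.6/√35 = 3.31 | 3.44 |
| One cadre, I-4 | 19 | 19.6/√19 = 4.50 | 4.82 |
| One cadre, both tiers | 54 | 19.6/√54 = 2.67 | 2.73 |
| One cadre, both tiers, weighted by facility share | 54 | 2.89 | 2.96 |

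The last row is the multiplier × √[(176/208)²×100/35 + (32/208)²×100/19].

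**6. One cadre within a tier, two-stage correction.** Put B = ICC + (1 − ICC)/M, where M is the mean number of providers of that cadre per facility (I-4: 564/32 = 17.6, 377/32 = 11.8, 394/32 = 12.3). For ICC 0 to 0.3, I-4 runs from about ±4.0 (z, ICC 0.3) to ±4.7 (t, ICC 0). I-3 runs from ±3.1 to ±3.4.

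**7. All cadres pooled within a tier.** I-4 has 19×3 = 57 providers. With the correction on the between-facility part only, the variance is (100/19)[ICC(1 − 19/32) + (1 − ICC)/3]. Using t with 18 df (2.10):

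| ICC | With correction | Without correction, 100(1 + 2·ICC)/57 |
|---|---|---|
| 0 | 2.78 | 2.78 |
| 0.1 | 2.81 | 3.05 |
| 0.3 | 2.87 | 3.52 |

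The corrected value stays within ±3 up to an ICC of about 0.74. Pooled I-3 (105 providers) is ±2.0 to 2.5 without any correction (t, ICC 0 to 0.3).

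**The case against.** The strongest reply is that the plan never expressly promises ±3% for a cadre within a tier. It speaks of three samples, one per cadre, so the word tier may be a slip for provider type. On that reading 54 per cadre meets the target without any correction. Read literally as providers of all kinds in a tier, the design supplies 105 and 57, both at least 54. The study is descriptive, no power claim rests on this number, the table and total fix the counts, and reported intervals would come from the observed data.

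Most of this stands. A reader might infer that ±3% is missed on every reading, even with cadres pooled in I-4. The documents do not support that: per cadre over both tiers it is met, and the pooled I-4 figure passes ±3 only if the reduction from sampling 19 of 32 facilities is ignored and the ICC is about 0.1 or more (t).

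A reader might also take the finite-population correction as something the plan states and should delete. It appears nowhere. The match to 35/19 is persuasive, but a bare 54 also follows from a 20% non-response allowance (42.68/0.8 = 53.35, rounded up), although that does not yield the split.

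The reply does not rescue the sentence. It disagrees with its table for any single cadre, its inputs do not give 54, and it leaves open which estimate carries the ±3%.

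**Conclusion.** The sample-size sentence is wrong as written, and the precision claim needs a defined target. The ±3% is supported for each cadre over I-3 and I-4 combined, and probably for all cadres pooled within a tier. It is not supported for one cadre within one tier: I-3 is wider than stated by about a tenth (3.31/3 = 1.10) and I-4 by 50 to 60% (4.50/3 = 1.50; 4.82/3 = 1.61). A two-stage correction narrows the I-4 gap without closing it.

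These figures rest on SD 10%, an assumed 95% level and an assumed ICC range. At 90% confidence one cadre in I-3 would meet the target (±2.78) and in I-4 would not (±3.77). That the plan used a facility-count correction is an inference from the matching split. None of this shows that the study needs more providers.

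**What to change.** In section c. Sampling, replace the per-tier statement with: 54 providers per cadre over both primary tiers (35 in I-3, 19 in I-4). In the same paragraph:

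- State the confidence level.
- State that ±3% is claimed per cadre over I-3 and I-4 combined, giving the expected ±2.7, or ±2.9 to 3.0 if tiers are weighted by facility share.
- Give the expected half-widths for one cadre within a tier, about ±3.4 in I-3 and ±4.8 in I-4 (t, SD 10%), without relying on a facility-count correction.
- Show the formula behind 35 and 19. If a finite-population correction was used, name it and justify it for a design that observes one provider per cadre per facility.

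The cost is wording only. The sample stays at 56 facilities and 192 observations; the stated tier-level precision becomes less favourable.

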#### **d. Recruitment and training of field workers** (enumerators and supervisors)

We will recruit experienced field workers, preferably with past exposure to health work, to become our enumerators and supervisors; this may include health workers with research experience. Training will be performed during a two-week period, which will include the methodology of the study, use of cell phones/tablets for the collection and transmission of the data in real-time, ethics in research, research integrity and a practicum. We will recruit 16 enumerators and 3 supervisors. As we have done before we will recruit in the training more participants than those needed, so we could choose those with better performance and just in case have people prepared if some of the field workers fail. All the trainees will participate in the pilot phase.

#### **e. Data collection**

We will coordinate closely with the Ministry of Health and authorities for the implementation of the study to ensure minimal disruption to clinical care.

1 e.1 A supervisor will perform an unannounced visit to the health center on random days  
2 in order to check for absences. This will allow us to obtain unbiased estimates of health  
3 worker attendance. The study team will attempt to locate a randomly selected subset of  
4 health workers expected to be in attendance during the time of the visit and will note his  
5 or her activity if located.

6  
7 e.2 One the day of the unannounced visit, the study team supervisor will confirm the shift  
8 schedule for that week and draw the shift sample for the full assessment based on times  
9 patient care is being actively provided. Consent will be obtained from the facility director  
10 prior to the visit. Consent will be obtained from the individuals sampled on the day of the  
11 visit prior to the start of observation. At the end of the observation protocol or the next  
12 day, the enumerator would apply the skills-questionnaire to each provider and to the  
13 director of the health center/hospital. That questionnaire would last no more than 20  
14 minutes.

15  
16 e.3 The supervisor will monitor the activities and productivity of enumerators  
17 corresponding to a DIRIS. They will also perform the surveys to the directors of the DIRIS.  
18 All the data will be collected with cellphones/tablets in real time; devices will include built-  
19 in range and consistency checks to ensure high data quality. The data manager will  
20 perform spot checks for data collection from each field team immediately after field visits  
21 and will notify the supervisor in cases of missing or erroneous data rates of >5%.

## 22 23 **f. Data analysis and report**

### 24 **f.1 Provider skill assessment**

25 Provider self-assessment of skills and identification of necessary skills will be summarized  
26 using descriptive statistics overall, within tier of facility, and within provider cadre.  
27 Differences between groups will be tested using the Kruskal-Wallis test for equality of  
28 distributions or Chi squared test for differences in proportions based on the selected  
29 variable type. Analysis will seek to identify the most important skills providers selected,  
30 the current capacity of providers in these areas, and any differences between  
31 perspectives based on cadre, facility tier, or other salient provider characteristics. Health  
32 facility directors will be classified as a unique group to enable consideration of their  
33 perspectives. Predictors of identification of specific skills can be assessed with  
34 multivariable regression as appropriate.

### 35 36 **f.2 Time and motion study**

37 Time spent per task will be summarized using descriptive statistics (e.g. mean, median,  
38 interquartile range); task predominance will be ranked within sub-groups. Outlying  
39 providers and facilities will be identified using data visualizations as well as descriptive  
40 statistics. Differences between groups such as facility tier and provider cadre will be  
41 tested using the Kruskal-Wallis test for equality of distributions or t-tests as appropriate,  
42 with multivariate regression (generalized estimating equation models to account for  
43 repeated sampling within facilities) applied as needed to control for individual covariates  
44 in identifying determinants of time use.

1 The final report will provide visual and quantitative descriptive results from both  
2 instruments.

3  
4 **Ethical Aspects**

5 The protocol and instruments will be presented for review and approval to the ethics  
6 committee of the Universidad Peruana Cayetano Heredia. The study will be discussed  
7 with the Ministry of Health authorities to get their support to avoid having to go through  
8 each health establishment ethics approval. We will ask for an exception of approval for  
9 the first observation but will require inform consent for the direct observation of the  
10 provider by the director of the center and by the provider itself. We will require a separate  
11 consent for the skills survey.  
12  
13

1 STROBE Statement—Checklist of items that should be included in reports of *cross-sectional studies*

| STROBE Statement – Checklist of items that should be included in reports of cross-sectional studies |         |                                                                                                                                                                                                              | Page No |
|-----------------------------------------------------------------------------------------------------|---------|--------------------------------------------------------------------------------------------------------------------------------------------------------------------------------------------------------------|---------|
|                                                                                                     | Item No | Recommendation                                                                                                                                                                                               |         |
| Title and abstract                                                                                  | 1       | (a) Indicate the study’s design with a commonly used term in the title or the abstract                                                                                                                       | 1       |
|                                                                                                     |         | (b) Provide in the abstract an informative and balanced summary of what was done and what was found                                                                                                          | 1-2     |
| Introduction                                                                                        |         |                                                                                                                                                                                                              |         |
| Background/rationale                                                                                | 2       | Explain the scientific background and rationale for the investigation being reported                                                                                                                         | 4-5     |
| Objectives                                                                                          | 3       | State specific objectives, including any prespecified hypotheses                                                                                                                                             | 6       |
| Methods                                                                                             |         |                                                                                                                                                                                                              |         |
| Study design                                                                                        | 4       | Present key elements of study design early in the paper                                                                                                                                                      | 6       |
| Setting                                                                                             | 5       | Describe the setting, locations, and relevant dates, including periods of recruitment, exposure, follow-up, and data collection                                                                              | 6       |
| Participants                                                                                        | 6       | (a) Give the eligibility criteria, and the sources and methods of selection of participants                                                                                                                  | 7-8     |
| Variables                                                                                           | 7       | Clearly define all outcomes, exposures, predictors, potential confounders, and effect modifiers. Give diagnostic criteria, if applicable                                                                     | 9-11    |
| Data sources/ measurement                                                                           | 8*      | For each variable of interest, give sources of data and details of methods of assessment (measurement). Describe comparability of assessment methods if there is more than one group                         | 9-10    |
| Bias                                                                                                | 9       | Describe any efforts to address potential sources of bias                                                                                                                                                    | 7-8     |
| Study size                                                                                          | 10      | Explain how the study size was arrived at                                                                                                                                                                    | 7       |
| Quantitative variables                                                                              | 11      | Explain how quantitative variables were handled in the analyses. If applicable, describe which groupings were chosen and why                                                                                 | 11      |
| Statistical methods                                                                                 | 12      | (a) Describe all statistical methods, including those used to control for confounding                                                                                                                        | 12      |
|                                                                                                     |         | (b) Describe any methods used to examine subgroups and interactions                                                                                                                                          | NA      |
|                                                                                                     |         | (c) Explain how missing data were addressed                                                                                                                                                                  | 11-12   |
|                                                                                                     |         | (d) If applicable, describe analytical methods taking account of sampling strategy                                                                                                                           | 7, 12   |
|                                                                                                     |         | (e) Describe any sensitivity analyses                                                                                                                                                                        | NA      |
| Results                                                                                             |         |                                                                                                                                                                                                              |         |
| Participants                                                                                        | 13*     | (a) Report numbers of individuals at each stage of study—eg numbers potentially eligible, examined for eligibility, confirmed eligible, included in the study, completing follow-up, and analysed            | 13-14   |
|                                                                                                     |         | (b) Give reasons for non-participation at each stage                                                                                                                                                         | 15      |
|                                                                                                     |         | (c) Consider use of a flow diagram                                                                                                                                                                           | NA      |
| Descriptive data                                                                                    | 14*     | (a) Give characteristics of study participants (eg demographic, clinical, social) and information on exposures and potential confounders                                                                     | 13-14   |
|                                                                                                     |         | (b) Indicate number of participants with missing data for each variable of interest                                                                                                                          | 15      |
| Outcome data                                                                                        | 15*     | Report numbers of outcome events or summary measures                                                                                                                                                         | 15-16   |
| Main results                                                                                        | 16      | (a) Give unadjusted estimates and, if applicable, confounder-adjusted estimates and their precision (eg, 95% confidence interval). Make clear which confounders were adjusted for and why they were included | 20      |
|                                                                                                     |         | (b) Report category boundaries when continuous variables were categorized                                                                                                                                    | NA      |

|                          |    |                                                                                                                                                                            |       |
|--------------------------|----|----------------------------------------------------------------------------------------------------------------------------------------------------------------------------|-------|
|                          |    | (c) If relevant, consider translating estimates of relative risk into absolute risk for a meaningful time period                                                           | NA    |
| Other analyses           | 17 | Report other analyses done—eg analyses of subgroups and interactions, and sensitivity analyses                                                                             | NA    |
| Discussion        |    |                                                                                                                                                                            |       |
| Key results              | 18 | Summarise key results with reference to study objectives                                                                                                                   | 20-21 |
| Limitations              | 19 | Discuss limitations of the study, taking into account sources of potential bias or imprecision. Discuss both direction and magnitude of any potential bias                 | 23    |
| Interpretation           | 20 | Give a cautious overall interpretation of results considering objectives, limitations, multiplicity of analyses, results from similar studies, and other relevant evidence | 23-24 |
| Generalisability         | 21 | Discuss the generalisability (external validity) of the study results                                                                                                      | 23-24 |
| Other information |    |                                                                                                                                                                            |       |
| Funding                  | 22 | Give the source of funding and the role of the funders for the present study and, if applicable, for the original study on which the present article is based              | 27    |

\*Give information separately for exposed and unexposed groups.

**Note:** An Explanation and Elaboration article discusses each checklist item and gives methodological background and published examples of transparent reporting. The STROBE checklist is best used in conjunction with this article (freely available on the Web sites of PLoS Medicine at <http://www.plosmedicine.org/>, Annals of Internal Medicine at <http://www.annals.org/>, and Epidemiology at <http://www.epidem.com/>). Information on the STROBE Initiative is available at [www.strobe-statement.org](http://www.strobe-statement.org).

1 Table S1: Tiers of health facilities within primary care in Lima

| Tier | Main services provided                                                                                                                       | Minimum staffing                                                                                |
|------|----------------------------------------------------------------------------------------------------------------------------------------------|-------------------------------------------------------------------------------------------------|
| I-1  | Preventive health services, minor illness, community visits                                                                                  | Nurse, nurse technician, midwife                                                                |
| I-2  | Outpatient and preventive health services                                                                                                    | Doctor, nurse, nurse technician, midwife                                                        |
| I-3  | Outpatient and preventive health services, laboratory services. Can include uncomplicated deliveries.                                        | Doctor, nurse, midwife, nurse technician, and laboratory technician                             |
| I-4  | Outpatient and preventive health services including pediatric and obstetric morbidities, laboratory services, maternity ward, emergency room | Pediatrician, gynecologist, doctor, nurse, midwife, nurse technician, and laboratory technician |

2

3

1 Figure S1: Dimensions, categories and subcategories for the observation protocol, doctors

